#### Eligibility Criteria

The inclusion and exclusion criteria stated below were refined during the feasibility trial [74] to maximise real world applicability to the individuals comprising the prisoner population who are identified to be at risk of suicide and seeking a psychological intervention. The inclusion criteria are (i) person sentence to imprisonment in a male prison, (ii) aged 18 years or over, (iii) at current risk of suicide behaviour as indicated by currently being on the host prison’s ACCT system, or on the ACCT system within the four weeks prior to consent, (iv) able to complete a brief battery of self-report measures with breaks if needed, and (v) willing to consent to being subject to a ‘holding order’ to require them to remain within the host prison for the duration of their participation in the trial. The exclusion criteria are (i) planned release within the next 9 months, (ii) insufficient knowledge of English to enable adequate participation in the assessment process, (iii) deemed by prison staff to be too dangerous/elevated risk of harm to the researcher, and (iv) considered by researcher to be lacking capacity to provide informed consent, according to the British Psychological Society’s code of human research ethics.

(http://www.bps.org.uk/sites/default/files/documents/code_of_human_research_ethics.pdf).

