To achieve a target sample size of *n* = 250, and accounting for expected attrition of up to 30% [74], a total of 360 participants will be recruited with recruitment split in proportion to the prison capacity of each of the host sites. According to our pilot RCT, we can also estimate 40% of people will decline to take part and a further 10% will be excluded for security reasons, therefore approximately 670 potential participants will be screened to determine eligibility (see Fig. 1).

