##### Duration of the PROSPECT Programme

Commencing after randomisation, delivery of the PROSPECT programme consists of up to 20 therapy sessions, delivered across a 6-month therapy window, with each 1:1 therapy session typically lasting 30 to 60 min. As shown in the PROSPECT Therapy Session Planner (see Fig. 2), the initial preparatory phase takes place over the first 6 sessions, with the CBSP phase delivered from session 6 through to session 20. This session planner should only be seen as a guide for the practitioner, with differences expected across patients as delivery is tailored according to individual needs. Nonetheless, specific sessions will be dedicated to the required tasks/techniques within both the preparatory phase and the CBSP phase. For example, within the CBSP phase, up to 5 sessions are assigned to the delivery of each specific therapeutic technique (e.g. appraisal restructuring). This is in accordance with the evidence base for each technique listed. The session planner recognises the opportunity to deliver multiple therapeutic techniques within a given session thus offering a more comprehensive targeting of the psychological architecture behind the patient’s suicidal thinking. However, this approach also presents a limiting factor since an excessive number of techniques being delivered within a single session is likely to undermine the focus of the session, confuse the patient, and so reduce potential for benefit. As such, we have learned to limit the concurrent delivery of therapeutic techniques to no more than 3 techniques within a single session. This delivery format for the PROSPECT programme is consistent with our previous and ongoing trials of psychological therapy to suicidal patients, within inpatient and community settings [33, 36, 83].

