### End of trial

The trial will end after the last patient recruited at baseline has completed the 6 month (window of 5–9 months) follow up. The declaration of end of trial will be submitted to REC within 90 days of its completion. Following this, all sites will be advised on the process for closing the trial at sites.

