Primary analysis of suicide ideation (BSSI) measured at 6 months (window 5–9 months) will use a linear mixed model with adjustment for baseline BSSI, stratification criteria and prognostic baseline covariates. The adjusted mean differences will be presented with 95% confidence intervals. BSSI is expected to be positively skewed and so the standard error and confidence interval for the treatment effect will be estimated by applying a bootstrap procedure [25] using the percentiles based on the results of 5000 replications (using the trial participant as the sampling unit). Primary analysis of suicidal behaviours (SB) measured within 6 months from randomisation will use a mixed model for count outcomes. The appropriate model with be chosen depending on the distribution of this variable. Analysis will adjust for baseline BS, stratification criteria and prognostic baseline covariates. The adjusted incident rate ratio will be presented with 95% confidence intervals. Due to the hierarchical ordering of these primary outcomes, no confirmatory claims can be made with regards to treatment benefit on SB unless it has first been demonstrated on BSSI. Secondary outcomes will be assessed using linear mixed models with similar adjustments. Analysis of primary and secondary outcome measures will be by intention to treat and will therefore include outcomes for all randomised participants in the group to which they were allocated, regardless of protocol adherence.

A therapeutic dose response model will be used to assess the effect of time engaged in therapy on treatment benefit. A complier average causal effect (CACE) model will be used to examine the treatment effect in those defined as ‘compliers’. Compliance will be defined from practitioner notes as a participant having started the ‘CBSP Phase’ of therapy. Treatment effect will be estimated within the subgroups defined by whether a participant has a history of suicide (Yes/No). As the study was not powered to investigate subgroup effects, this will be a purely exploratory analysis. All inferential analyses will adjust for stratification factors used in randomisation. Additionally, baseline outcome and prognostic variables will be adjusted for to improve power. Where outcome variables are skewed, bootstrapped confidence intervals will be presented. There will be no interim analysis of outcome data during the trial.

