### Safety reporting

#### Adverse Events (AEs)

An adverse event (AE) reporting system will be used on the trial. Suicidal ideation, self-harm, harm to others and property will be routinely recorded and it is expected that these will occur for some participants. These will include, ideation alone with no behaviour (suicidal ideation or self-harm ideation), self-harm or suicidal behaviour (cutting self, biting and breaking the skin, severely scratching or running anything on the skin, using corrosive substances on the skin, sticking sharp objects into the skin, pulling out hair, burning with a cigarette lighter or match, scolding the skin, swallowing objects, choking or blocking airways, inserting objects into body cavities, overdosing with prescribed medication, overdosing with non-prescribed medication, taking illicit substances (not including medication), taking poisonous substances, inducing vomiting, over-eating, eating something that is known to cause an allergic reaction, food or fluid refusal, refusing medication, violence towards an inanimate object (e.g. a wall or door), ligaturing/hanging, drowning, severing body parts, electrocuting), events involving others (threats to harm others / violence, actual harm to others / violence). It should be noted that these may be Serious Adverse Events (SAEs) depending on the severity of injuries and outcomes of the behaviour. These events do not require further follow up unless there is evidence that these are research related but each event should be recorded from consent until 1 month after the final follow-up assessment is completed. Any untoward medical occurrence that is not included in the definition above will not be reported.

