#### Serious Adverse Events (SAEs)

All SAEs occurring from the time of consent until 1 month after the final follow-up assessment completion will be recorded on the SAE report form and emailed to the Prospect Trial Manager and CI (as sponsor’s representative) immediately and within 24 h of the research staff becoming aware of the event. Any change of condition or other follow-up information will be reported to the Trial Manager and CI as soon as it is available, or at least within 24 h of the information becoming available. Events will be followed up until the event has resolved or a final outcome has been reached.

The Trial Manager and CI will review the SAE form. If the SAE is related to participation in the trial, the CI will review the expectedness in relation to the nature or severity of which is not consistent with the effects or consequences of participation in a psychological intervention trial. All adverse events that are research related will be reported by the CI to the relevant host prison responsible clinical team and the Data Monitoring and Ethics Committee (DMEC) on a regular basis and in an expedited fashion. Fatal or life-threatening events will be reported to the Programme Steering Committee, the DMEC and the relevant Ethics Committee within seven days of knowledge of such cases.

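### AE and SAE recording ends one month after a follow-up assessment that may fall at months 5 to 9 or never take place, so observation time varies and the between-arm safety comparison could be distorted

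*Protocol article*

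**What the plan says.** All references are to the protocol article.

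- **Adverse Events (AEs):** "each event should be recorded from consent until 1 month after the final follow-up assessment is completed".
- **Serious Adverse Events (SAEs):** the same anchor, for "All SAEs occurring from the time of consent until 1 month after the final follow-up assessment completion".
- **End of trial:** the trial closes once the last participant "has completed the 6 month (window of 5–9 months) follow up". Data analyses of the RCT repeats the window: "Primary analysis of suicide ideation (BSSI) measured at 6 months (window 5–9 months". This is the only post-baseline assessment of outcomes, so it is also the final one.
- **Duration of the PROSPECT Programme:** therapy consists of "up to 20 therapy sessions, delivered across a 6-month therapy window", starting after randomisation.
- **Sample size calculation:** the recruitment target is set "accounting for expected attrition of up to 30" per cent.
- **Monitoring of adverse events:** the steering committee may be alerted to consider recommending early discontinuation if the IDMC sees an inflated rate of suicide-related events in the active arm relative to control that is attributable to taking part.
- **Co-primary outcomes:** by contrast, suicidal behaviour is counted over 6 months from randomisation for every participant.

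**The concern.** The end of safety recording depends on something that happens after randomisation: when, and whether, the participant is interviewed. Two consequences follow.

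First, participants are watched for different lengths of time. Someone interviewed at month 5 leaves observation at month 6, as the therapy window ends. Someone interviewed at month 9 is watched for four months beyond it.

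Second, the rule names no end date for a participant who never completes the assessment. The article does not say whether recording then runs on, stops at last contact or stops at some other date, and sites could apply it differently.

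What is at stake is the between-arm comparison of suicide-related events in a high-risk population. If timing or completion of the assessment differed by arm, a difference in event counts would mix risk with length of observation. The efficacy analyses are not affected.

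**Working it through.** **Inputs.** Assessment window 5 to 9 months, nominal 6 (End of trial; Data analyses of the RCT). Recording continues 1 month after assessment (AE and SAE sections). Therapy window 6 months (Duration of the PROSPECT Programme). Attrition up to 30%, analysis set 250, recruitment 360 (Sample size calculation). I take months as counted from randomisation; the time from consent to randomisation adds a little for everyone.

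**1. The plan's own figure.** Recruitment = analysis set / (1 − attrition) = 250 / 0.70 = 357.1, rounded up to 358. The protocol states 360, so the figure is reproduced.

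**2. Length of the recording window.** Close of recording = assessment month + 1.

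| Assessment at month | Recording closes at month | Months past the therapy window |
|---|---|---|
| 5 | 6 | 0 |
| 6 (nominal) | 7 | 1 |
| 9 | 10 | 4 |

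The longest-to-shortest ratio between two individuals is 10 / 6 = 1.67.

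**3. Participants with no stated end date.** At the planning ceiling, 0.30 × 360 = 108. At 10% attrition it would be 36, and at zero none.

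**4. Effect on an arm comparison.** Let the true event rate be equal and constant in both arms, and let the mean assessment month be *a* in one arm and *b* in the other. Among assessed participants the expected ratio of event counts is (*b* + 1) / (*a* + 1).

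| Mean month *a* v *b* | Calculation | Ratio |
|---|---|---|
| 6 v 6 | 7 / 7 | 1.00 |
| 6 v 6.5 | 7.5 / 7 | 1.07 |
| 6 v 7 | 8 / 7 | 1.14 |
| 6 v 8 | 9 / 7 | 1.29 |
| 5 v 9 | 10 / 6 | 1.67 |

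The timing differences are assumptions chosen to show scale; the document reports none. The last row needs every participant in one arm at the earliest permitted date and every participant in the other at the latest, so it is a bound and not a scenario.

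**5. With a common window.** If every participant is compared over the same nominal length from randomisation, the exposure ratio is 1.00 whatever the interview dates, provided events are ascertained to the end of that window.

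**The case against.** The strongest case against is that one recording rule covers both arms, randomisation is individual and stratified, and assessors are blind to allocation. Unequal windows between individuals then add noise, not bias. That stands. A reader might infer that arm-level safety counts are simply not comparable; the document does not support this, because it shows no difference by arm in interview timing or attrition.

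Other parts of the objection also stand:

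- The 30% is a planning ceiling, so it cannot be read as the known share never interviewed. Participants who are transferred or released are to be followed up.
- Closing exactly as therapy ends needs an assessment at the earliest permitted date. At nominal month 6 there is one further month.
- Suicidal behaviour, the main expected harm, already has a fixed 6-month count as a co-primary outcome.
- A reader might infer a conflict between recording to month 10 and the exclusion of "planned release within the next 9 months". There is none, since a post-release follow-up procedure is described.

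It can also be said that the monitoring section speaks of a rate, that person-time rates would handle unequal windows, and that a cut-off for non-attenders may sit in the full protocol or a safety procedure not shown. This helps only in part. Person-time needs an end date, and the stated rule supplies none for those never assessed. Nor does it equalise which months are observed: some participants contribute post-therapy time and others do not. The point rests on the rule as the article states it, not on the absence of a detail.

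**Conclusion.** The point holds in a limited form. As written, AE and SAE recording closes between month 6 and month 10 depending on the interview date, and has no stated end for participants never assessed (up to about 108 of 360 at the planning ceiling). The between-arm rate used for monitoring may be distorted if timing or attrition differs by arm: about 7% for a half-month and 14% for a one-month difference in mean timing, and nothing if timing and attrition are the same. Those percentages assume a constant event rate, equal in both arms, and describe assessed participants only. The document gives no evidence that such a difference will occur. This is an avoidable weakness that should be corrected; it does not show that the safety comparison is invalid.

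**What to change.** Keep recording AEs and SAEs from consent as now. Add one fixed comparison window, anchored to randomisation, that applies to all participants in both arms whether or not they are assessed. Two lengths fit the protocol's own figures:

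- **7 months**, the nominal 6 + 1. Anyone assessed before month 6 would need ascertainment extended to month 7, because the present rule closes earlier for them.
- **6 months**, matching the suicidal behaviour co-primary outcome. Every assessed participant is already covered to at least month 6, so only non-attenders need extra work.

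For non-attenders, complete the window from the prison and clinical records to which access is already planned subject to consent (Demographic, clinical and criminological data), leaving out anyone who has withdrawn consent for use of their data (Consent and eligibility). Researchers are kept from full clinical notes until final assessments are done, so this check is best made after the month-9 limit has passed. Report events beyond the fixed window separately, outside the between-arm comparison.

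The cost is a change of wording and a record check for non-attenders. Later events leave the comparative table, but they are still recorded and reported, so no safety information is lost.

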#### Serious Adverse Events (SAEs)

All SAEs occurring from the time of consent until 1 month after the final follow-up assessment completion will be recorded on the SAE report form and emailed to the Prospect Trial Manager and CI (as sponsor’s representative) immediately and within 24 h of the research staff becoming aware of the event. Any change of condition or other follow-up information will be reported to the Trial Manager and CI as soon as it is available, or at least within 24 h of the information becoming available. Events will be followed up until the event has resolved or a final outcome has been reached.

The Trial Manager and CI will review the SAE form. If the SAE is related to participation in the trial, the CI will review the expectedness in relation to the nature or severity of which is not consistent with the effects or consequences of participation in a psychological intervention trial. All adverse events that are research related will be reported by the CI to the relevant host prison responsible clinical team and the Data Monitoring and Ethics Committee (DMEC) on a regular basis and in an expedited fashion. Fatal or life-threatening events will be reported to the Programme Steering Committee, the DMEC and the relevant Ethics Committee within seven days of knowledge of such cases.

#### Monitoring of adverse events

Due to the nature of the participant sample, it is anticipated that a number of suicide-related adverse events (expression of suicidal ideation, intent, behaviours and attempts) will occur in both the active and control arms of the research trial. As stated, suicidal behaviour is one of the primary outcome measures of this study. However, should the IDMC become aware of an inflated rate of suicide-related adverse events in the active, relative to the control, arm of the trial that is attributable to participation in the trial, then the PSC may be alerted to consider recommending a premature discontinuation of the trial (Duggan et al., 2014).

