#### Methods to protect against sources of *bias*

The following measures will be put in place to protect against potential sources of bias. An independent third party will perform the randomisation of participants to the trial arms which protects against allocation bias. Randomisation will take place only when potential participants have consented to participate and baseline data has been collected and data entered onto the eCRF. Researchers performing the assessments will be blind as to the participant’s treatment allocation with precautionary strategies employed to prevent the researcher from becoming unblinded which will include (i) practitioners to consider room use and diary arrangements in light of potential breaks of masking; (ii) participant reminded by researcher not to talk about treatment allocation, and (iii) researcher to be prevented sight of participant’s full clinical notes until final assessments have been completed. In order to maintain the blind, therapy only assessments will be undertaken by the practitioners delivering the intervention and recorded on separate eCRF which will not be accessible or visible to the researchers. Blind breaches and potential blind breaches will be recorded and monitored and where possible another researcher will undertake follow-up assessments in replacement of a researcher that has become unblinded. All variables have been defined prior to the RCT taking place. Intention-to-treat analyses will be used. Participant throughput will be recorded, e.g., reasons potential participants opted not to participate. Reasons why participants dropped out of the trial will be recorded, if available. The CTU will set-up and manage electronic data capture for all RCT data required for analysis. The research team will undertake appropriate reviews of the entered data.

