This trial may actually benefit individual participants since cognitive behavioural therapies are not routinely available for suicidal patients in prison. Furthermore, all participants taking part in this trial, in both the PROSPECT therapy programme plus TAU and the TAU alone groups, will receive an enhanced level of monitoring such that any participant deemed to be at suicidal risk will be identified and immediately directed to appropriate care available within the host institution. Our feasibility trial with this patient group reported a modest benefit of entering the TAU condition, likely due to the additional monitoring and sensitive manner of the research assessors [74]. No treatments will be withheld during the trial, with all participants having access to the support they were receiving before the research study (e.g. Prison GP, Mental Health Team, Drug & Alcohol Team), so there is no expected disadvantage in taking part. Participants will not receive payment for participating in the trial, but assurances will be sought from the host prison governor that participants will be authorised to miss their usual work responsibilities in order to attend therapy or research appointments without affecting their usual wage.

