### Researcher risk management

All members of the research team, which includes practitioners and RAs, will abide by the lone working policies of their employer(s). For the aspects of the research that take place in a prison setting, the research team will undertake the necessary induction training and security clearances as determined by the individual prison and will abide by the health and safety policies and procedures of the prison. A risk assessment for the study has been conducted and a researcher safety protocol is in place that all research staff will be familiar with prior to undertaking research activities. All researchers will receive clinical supervision on a fortnightly basis and will be able to speak to the CI or Programme/Trial Manager between clinical supervision sessions.

There is a possibility that research participants may tell the researcher information that the researcher will have a duty to disclose to the appropriate authorities. Participants will be informed via the Participant Information Sheets that the researchers may have to disclose any information that raises concerns about participant safety or the safety of others, information regarding undisclosed illegal acts or any current plans of future illegal activities behaviour that is against the prison rules, or information that raises concerns about terrorist, radicalisation or security issues. Additionally, prison staff or other professionals taking part in the research will be informed that researchers will have a duty to inform the appropriate authorities should they disclose information about misconduct or poor practice.

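### The between-arm comparison of suicide-related adverse events is open to differential detection, because the active arm has an extra channel through which events become known

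*Protocol article*

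**What the plan says.** All from the Protocol article.

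- **The trigger** (Monitoring of adverse events). The committee is to look for an "inflated rate of suicide-related adverse events in the active, relative to the control, arm of the trial". The excess must also be judged to result from taking part. The consequence is worded permissively: "then the PSC may be alerted to consider recommending a premature discontinuation of the trial". The events listed there run from expressed ideation and intent to behaviours and attempts. No numerical threshold is given.
- **How events enter the record.** The Adverse Events section has events recorded from consent until one month after final follow-up, in the same words for both arms, without naming a source. Serious events are reported "within 24 h of the research staff becoming aware of the event" (Serious Adverse Events).
- **Who is research staff.** The section on Researcher risk management refers to "All members of the research team, which includes practitioners and RAs".
- **Contact in the active arm.** The programme consists of "up to 20 therapy sessions, delivered across a 6-month therapy window". The pilot mean was 9 sessions, and over 70% attended five or more (Fidelity measures). Therapists also consider withdrawal from therapy after suicidal behaviour, hospitalisation for suicidal crisis or a clinically significant rise in ideation (Drop-out from trial intervention criteria).
- **Contact common to both arms.** Outcomes are assessed at baseline and 6 months (Abstract). Assessing researchers may not see a participant's "full clinical notes until final assessments have been completed".
- **Other routes common to both arms.** Participants in both groups "will receive an enhanced level of monitoring such that any participant deemed to be at suicidal risk will be identified", with no frequency or means stated. The distress protocol applies at any encounter with the research team (Participant risk management). ACCT care is part of usual treatment. Prison and clinical records may be accessed with consent, serious self-injury being one example (Demographic, clinical and criminological data).

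**The concern.** A comparison of event rates between arms is interpretable only if an event of a given kind has the same chance of being recorded in each arm. Here one arm has regular one-to-one conversations about suicidal thinking with someone who belongs to the research team, and the other does not. Expressed ideation and intent are the events most dependent on contact, and they count towards the trigger.

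If the active arm shows more events, the committee cannot readily tell harm from closer listening. It could raise an alarm over an artefact, or become used to explaining an excess away and miss a real one. The published adverse event table would carry the same ambiguity. Events in the control arm that come to light late would also start the serious-event reporting clock late.

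**Working it through.** The documents give no event rate, detection rate or threshold, so there is no stated figure to reproduce. The calculation below only illustrates direction and plausible size.

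**Inputs from the Protocol article**
- 360 randomised with equal allocation: 180 per arm.
- Attrition up to 30%: 0.7 reach the 6-month interview.
- Over 70% of pilot therapy participants attended five or more sessions: 0.7 taken as the share with real exposure to therapy.

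**Assumed inputs, shown as ranges**
- True event rates equal in the two arms.
- s, the share of events known through routes common to both arms: 0.4 to 0.8, with 1.0 as reference.
- q, the chance that an event not otherwise known is disclosed at a contact: 0.5 to 0.9.
- h, the share of otherwise unknown events revealed in therapy before the 6-month interview: 0.3 to 0.7.

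**Whole follow-up**

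Control detection: C = s + (1 − s) × 0.7q

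Active detection: A = s + (1 − s) × [1 − (1 − 0.7q)²]

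Example, s = 0.4 and q = 0.5: C = 0.4 + 0.6 × 0.35 = 0.610; A = 0.4 + 0.6 × (1 − 0.65²) = 0.4 + 0.6 × 0.5775 = 0.746; A/C = 1.22.

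| s | C (q = 0.5; 0.9) | A (q = 0.5; 0.9) | A/C |
|---|---|---|---|
| 1.0 | 1.000; 1.000 | 1.000; 1.000 | 1.00 |
| 0.8 | 0.870; 0.926 | 0.915; 0.973 | 1.05 |
| 0.6 | 0.740; 0.852 | 0.831; 0.945 | 1.11 to 1.12 |
| 0.4 | 0.610; 0.778 | 0.746; 0.918 | 1.18 to 1.22 |

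**Before the 6-month interview**

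If control events are so far known only through the common routes, the ratio is [s + (1 − s)h] / s.

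- s = 0.8: 0.86/0.80 to 0.94/0.80, about 1.07 to 1.17
- s = 0.6: 0.72/0.60 to 0.88/0.60 = 1.20 to 1.47
- s = 0.4: 0.58/0.40 to 0.82/0.40 = 1.45 to 2.05

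**Chance of a nominally significant active-arm excess**

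This uses the whole-follow-up model with 180 per arm, a two-sided 0.05 comparison of proportions and a single look. The chance would be 2.5% with equal detection.

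| s | true proportion with an event 20% | 40% |
|---|---|---|
| 0.8 | about 4% | about 6% |
| 0.6 | about 7% | about 11% |
| 0.4 | about 11% | 20% to 21% |

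The event proportions are also assumptions. The protocol specifies no such test; the table only shows how often an artefact could look like a signal. In this model the ratio exceeds 1 whenever s is below 1, and returns to 1.00 when one common source captures every event.

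**The case against.** The tempting stronger reading is that control-arm events surface only at the 6-month interview, so that an active-arm excess is certain. Under that reading, take uniform recruitment of 360 over 21 months (8.57 per arm per month). By month 12 each arm has 51.4 × 6 + 51.4 × 3 = 462.9 person-months. Control sees 0.7 × 308.6 = 216.0 of them; therapy sees 388.8 (216.0 + 0.7 × 246.9) to 462.9. The apparent ratio is 1.80 to 2.14. The arithmetic is right, but the premise is an inference. The baseline and 6-month schedule says when outcomes are assessed, and is not a list of every contact. ACCT, consented records, enhanced monitoring and the distress protocol all serve both arms. The restriction on notes binds the assessing researcher and does not close off incident information to others. With s = 0.8 in the same model, control visibility is 0.8 + 0.2 × 216.0/462.9 = 0.893 and the ratio falls to about 1.08 to 1.12.

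Three further objections deserve weight.

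- The excess must be attributable to participation, and the steering committee only may be alerted. This softens the consequence. But attribution is judged on events already detected, so it cannot restore the control events that were missed.
- The IDMC also looks at outcome data (Trial management), and suicidal behaviour is collected alike in both arms by self-report with an adapted SASI. That is a useful cross-check on behaviours. It comes at follow-up, with up to 30% missing, and the trigger itself is written on adverse events.
- Ascertainment detail may sit in operating procedures that are not shown. That could supply the missing source. The point made here concerns the comparison as the article states it, which makes no allowance for unequal contact.

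**Conclusion.** The comparison should be amended. Practitioners give the active arm a detection channel that the control arm lacks, and the stated rule does nothing to equalise ascertainment. The routes shared by both arms dilute this difference without removing it. The bias in detection is upward in the active arm unless common capture is complete. It matters most for expressed ideation and minor events; serious incidents are more likely to be recorded alike.

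The size cannot be determined from the documents. The ratios and false-signal chances worked out above rest entirely on assumed capture and disclosure shares and on equal true rates. The documents do not support saying that an observed excess is built in, or that the rate ratio will be near 2. What the committee sees will also depend on the true treatment effect, on how well records cover events and on the attribution judgement.

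**What to change.** 1. Add a field to the adverse event and serious adverse event forms for how the event was detected: therapy session, research assessment, prison or healthcare record, staff report, other.
2. Base the between-arm rate in Monitoring of adverse events, and the headline adverse event comparison in the report, on events ascertained in the same way in both arms. One option is ACCT and prison incident records obtained at the same intervals for every participant by someone outside the blinded assessor team, read alongside the SASI count.
3. Give the IDMC a separate table of therapy-disclosed events. These stay fully reported and individually reviewed; only their place in the between-arm rate changes.

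None of this sets a threshold or alters when treatment or the trial would stop.

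The cost is one form field, record-extraction time and a short amendment. The main downside is that records capture ideation poorly, so the symmetric comparison would rest mainly on behaviours. That is why the separate table is needed and therapy-disclosed events should not simply be dropped.
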